Therefore, the following hypotheses will be operationalized: (i) individual with IDD increased physical fitness after 12 and/or 24 weeks of PE; (ii) individual with IDD increased general health after 12 and/or 24 weeks of PE; (iii) individual with IDD increased dementia/cognitive decline after 12 and/or 24 weeks of PE; (iv) individual with IDD increased QoL decline after 12 and/or 24 weeks of PE; (v) there was a difference between groups on levels of physical fitness after 12 and/or 24 weeks of PE; (vi) there was a difference between groups on levels of general health after 12 and/or 24 weeks of PE; (vii) there was a difference between groups on levels of dementia/cognitive decline after 12 and/or 24 weeks of PE; and (viii) there was a difference between groups on levels of QoL after 12 and/or 24 weeks of PE.

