## 2. Materials and Methods

### 2.1. Study Design

The present study protocol describes a non-randomized experimental study, consisting of three groups (1:1 allocation), to assess and compare the effectiveness of two different combined PE (strength + aerobic capacity) for individuals with IDD.

Participants will be allocated to one of the three groups: (i) indoor training group (IG) with sessions carried out in a gym, using weight machines; (ii) outdoor training group (OG) with sessions using low-cost materials; and (iii) control group (CG) with participants continuing to do their normal activities (participation in one of the exercise interventions will not be allowed), based on their interests and availability to be involved with PE programs.

Participants from both intervention groups will participate twice a week, in a 24-week supervised PE program, with sessions lasting 45 min per session. All outcome measures will be collected at three different time moments, at baseline (time 0, baseline assessment, or week 0), at mid-term (time 1, intermidiate assessment, week 12), and at the end of the intervention program time 2, final assessment, week 24). The measurements will be performed after 48 h, after the last workout in both groups, and always in the morning. Figure 1 shows the participant flow for this trial.

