### 2.5. Assignment of Intervention and Blindness

After obtaining informed consent and finishing the initial assessments, the volunteers will be distributed to the three groups, according to their intention to participate in the study. Due to the nature of the intervention, after the initial assessment, it will not be possible to randomize the sample by groups, nor will it be possible to “blind” the participants and lead investigator belonging to the group. Upon delivery of the informed consent, a code will be assigned to each participant, ensuring the anonymity of the subjects. The researchers responsible for the evaluations will have no knowledge of which group each subject belong to, except for the principal researcher. To minimize differences in procedures, the same team will perform the assessments at different moments.

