## 5. Procedures

Intervention study that involves several phases: (a) design of PE programs; (b) promotion of the program (information pamphlets will be distributed to the target people with IDD/guardians/tutors/caregivers about the study procedures and aims); (c) sample recruitment (participants/parents/tutors will sign an informed consent form and all project will be carried out in accordance with the Declaration of Helsinki; (d) division according to their intention to participate in the study: (i) IG/indoor context (using weight machines), (ii) OG (low cost), or (iii) CG (no specific intervention; continue with normal daily activities); (e) initial evaluation of the groups by an evaluator blinded to the group belonging; (f) intermidiate evaluation of the groups by an evaluator blinded to the group belonging; (g) final evaluation of the groups by an evaluator blinded to the group belonging; (h) data analysis: descriptive, comparison between groups and conditions, comparison before and after, correlations, among others (subjects who do not perform at least 75% of the sessions will be excluded from data processing).

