## 8. Statistical Analysis

In the statistical analysis, descriptive parameters will be used (mean ± standard deviation or percentage) normality and homogeneity will be verified through the *Shapiro*–*Wilk* test and the *Levene* tests, respectively. The existence of significant differences between groups will be analyzed using the *Kruskal*–*Wallis* test and between times using *Wilcoxon* or *Friedman* test. The non-parametric statistic was defined according to the “Central Limit Theorem” [63], in the sense that it will require 30 participants in the sample to have a normal distribution. The magnitudes of the differences will be examined using the *Cohen’s d* effect size [64]. Likewise, associations across studies variables will be verified through the *Spearman* coefficient of bivariate correlations (*r* = 0.10 to 0.29—small; *r* = 0.30 to 0.49—moderate; *r* = 0.50 to 1—strong) [65]. The significance level adopted for all analyses will be *p* < 0.05. For data processing, the computer program *Statistical Package for Social Sciences* (SPSS Science, Chicago, IL, USA), version 28 will be used.

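### As written, no planned test compares change between groups or adjusts for baseline, so in self-selected groups of about 7, pre-existing differences can be read as programme effects

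*Protocol article*

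**What the plan says.** **Tests.** Section 8 (Statistical Analysis) splits the analysis in two. For groups: "The existence of significant differences between groups will be analyzed using the" Kruskal-Wallis test. For occasions: "and between times using" Wilcoxon or Friedman. Cohen's d and Spearman correlations complete the list. Section 5 (Procedures) repeats the split: "comparison between groups and conditions, comparison before and after, correlations, among others".

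**Reason given.** Section 8 justifies the non-parametric choice by the Central Limit Theorem, in that "it will require 30 participants in the sample to have a normal distribution".

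**Hypotheses.** Between-group hypotheses (v) to (viii) in the Introduction have this form: "there was a difference between groups on levels of physical fitness after 12 and/or 24 weeks of PE". The other three replace physical fitness with general health, cognitive decline and quality of life.

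**Allocation.** Section 2.1 forms the groups "based on their interests and availability to be involved with PE programs". Section 2.5 says that, after consent and the initial assessments, "the volunteers will be distributed to the three groups, according to their intention to participate in the study", and that "it will not be possible to randomize the sample by groups". Section 9 lists the lack of randomisation as a limitation but attaches no analytic remedy.

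**Sample size.** Section 2.2 fixes 21 participants and reports that at least 15 are needed for an effect size of 0.5, alpha 0.05 and power 0.95 in a repeated-measures ANOVA. Section 8 does not use that model.

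**The concern.** The main objective is to compare the effectiveness of two programmes. In a non-randomised study the natural comparison is of how much each group changed, or of follow-up values given the baseline. Every outcome is measured at week 0, before allocation, so the data for this exist.

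Neither kind of named test makes that comparison. A one-way rank test on follow-up values carries any starting difference straight into the result. A within-group paired test has no comparator, so it cannot separate training from practice on the tests or regression to the mean. Putting within-group results side by side is not a substitute for a between-group contrast.

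At stake are false positives when fitter or more motivated people choose exercise, and low power when they do not.

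**Working it through.** **1. The plan's own figure.** The article does not give the correlation, the sphericity correction or the effect-size metric. Assume f = 0.5, correlation ρ = 0.5 between occasions, no sphericity correction, 3 groups and m = 3 occasions, with N = 15.

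- Within-subject and interaction effects: λ = f²·N·m/(1 − ρ) = 0.25 × 15 × 3/0.5 = 22.5. Power is 0.984 for time (df 2, 24) and 0.948 for group-by-time (df 4, 24).
- Between-group main effect: λ = f²·N·m/(1 + (m − 1)ρ) = 11.25/2 = 5.625. Power is 0.449 (df 2, 12), and 45 participants would be needed for 0.95.

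So 15 is reproduced for a time effect, and to within rounding for group-by-time, but not for a difference in overall level between groups. The quoted power belongs to a kind of contrast that Section 8 does not name.

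**2. What each between-group analysis does with a baseline gap.** Let both exercise groups exceed control by d SD at baseline and follow-up, with no programme effect. Take equal SDs σ and baseline to follow-up correlation ρ.

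| Analysis | Spurious difference expected | Error variance per person |
|---|---|---|
| Follow-up level | d | σ² |
| Change from baseline | 0 | 2(1 − ρ)σ² |
| ANCOVA on baseline | (1 − ρ)d | (1 − ρ²)σ² |

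At d = 1, ANCOVA leaves 0.5 SD when ρ = 0.5 and 0.1 SD when ρ = 0.9. At ρ = 0.8 the variances are 1, 0.40 and 0.36 times σ². At ρ = 0.5 they are 1, 1 and 0.75, so change scores then gain no precision over levels.

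**3. Simulated rejection rates at nominal 0.05.** Groups of 21/3 = 7, bivariate normal data, no programme effect, ρ from 0.5 to 0.9. Both d and ρ are assumptions.

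| Gap d | Kruskal-Wallis, level | Kruskal-Wallis, change | ANCOVA |
|---|---|---|---|
| 0 | 4–5% | 4–5% | 5% |
| 0.5 SD | 12% | 4–5% | 5–7% |
| 1.0 SD | 37–38% | 4–5% | 6–14% |

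The upper ANCOVA figures are at ρ = 0.5. There, at d = 0.5, a 4,000-run batch gave 8% and a 20,000-run check gave 7%.

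**4. Precision lost.** With no imbalance and a true 0.5 SD benefit of both programmes, Kruskal-Wallis on levels has power 11–12%. ANCOVA has about 20%, 28% and 50% at ρ = 0.7, 0.8 and 0.9.

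**5. Within-group tests side by side.** If two groups change equally and each Wilcoxon test has power p, exactly one is significant with probability 2p(1 − p). With 7 per group and ρ = 0.7, simulation gives 39%, 48% and 34% for true changes of 0.5, 0.8 and 1.0 SD.

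**6. The stated rationale.** The Central Limit Theorem concerns the distribution of sample means. It does not make data normal at 30 participants, sets no threshold there, and gives no reason to leave out the baseline.

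**The case against.** **Levels are inferred.** Section 8 does not say whether Kruskal-Wallis is run on levels or on change. The word levels comes from the hypotheses, Section 5 leaves its list open, and Section 9 speaks of expected changes. If change was meant, the error rate in the illustration is already 4–5%. This stands as a limit on certainty. It does not close the gap, because no passage names a change score and the hypothesis wording points the other way.

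**Misreading is possible, not certain.** A reader might infer that baseline differences will be taken for programme effects, or that significance in one group only will be treated as a difference. The article says neither, and it declares non-randomisation as a limitation. A week-0 Kruskal-Wallis test could also reveal imbalance. That is a weak safeguard: in the same simulations (ρ = 0.5 and 0.8) it detects a 0.5 SD gap in 12–13% of trials and a 1 SD gap in 36–38%, and no rule says what would follow.

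**The objective is not left unanswered.** A reader might also conclude that it is. A three-group test with Cohen's d does compare the programmes, though inefficiently and open to confounding, in what the Discussion calls a pilot.

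**The scenario is chosen.** The gap is assumed, perfectly stable, and equal in both exercise groups. It therefore favours change scores by construction and does not quantify bias in indoor versus outdoor. This stands.

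**ANCOVA is not a full cure.** It leaves up to 14% under a stable 1 SD gap. Permutation or exact p-values also rest on exchangeability, which self-selection does not supply. This stands too, and it is why the fix does not insist on one model.

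**Separate faults.** The Central Limit Theorem sentence and the mismatch with the powered model do not in themselves show bias.

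**Conclusion.** The point holds in a limited form. The article commits to specific tests, and none of them, read with its hypotheses, is a between-group comparison of change or a baseline-adjusted contrast. This is more than detail left to an analysis plan, because the tests are named.

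Under an assumed stable gap of 0.5 to 1 SD between exercisers and control, false positives rise from about 5% to about 12–38% on follow-up levels. They stay near 5% on change. With no gap, the test on levels holds its error rate and the cost is power alone. The size of any real imbalance, and any bias between the indoor and outdoor groups, cannot be known from the document.

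**What to change.** - Name one main between-group analysis. Either compare change from baseline (for example Kruskal-Wallis on change with exact p-values), or fit a baseline-adjusted or group-by-time model, which would match the repeated-measures ANOVA behind the sample size.
- Report indoor versus outdoor, and each versus control, with 95% confidence intervals.
- Reword hypotheses (v) to (viii) to match the chosen contrast. If change was always intended, say so.
- Treat within-group Wilcoxon and Friedman results as descriptive.
- Delete the Central Limit Theorem sentence. Small samples and doubtful normality are reason enough for rank methods.
- State that adjustment reduces confounding by self-selection but does not remove it, notably for unmeasured motivation, and that ANCOVA can leave part of a stable gap uncorrected.

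The cost is wording and one additional analysis per outcome. Baseline values are already collected, so no new data or participants are needed. The choice should be fixed before any group comparison is seen.

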### 2.2. Participants

Adult volunteers, institutionalized in a support institution, located in Leiria, Portugal, recruited by the non-probabilistic convenience method will participate in the program.

In the first step, an individual explanation will be held about the procedures and objectives of the study, as well as the potential benefits, risks, and the time needed for the development of the project.

In a second moment, the participants/family members/tutors will sign a free consent form. Inclusion criteria will be defined: (1) adults with IDD, diagnosed with mild, moderate, or severe IDD; (2) age over 18 years) success in performing movements such as pulling/pushing; (3) capacity to perform the assessments. Exclusion criteria will be defined: (1) individuals who cannot commit themselves for 6 months; (2) individuals with other associated pathologies; (3) contraindications to PE (e.g., high blood pressure); (4) inability to walk unaided; (5) profound IDD; (6) inability to communicate; (7) non-delivery of signed informed consent.

Due to the characteristics of this special population and logistical constraints intrinsic to the development of intervention studies, the sample will consist of the first 21 individuals who agree to participate in the program, aged between 18 and 65. After that, participants will be allocated to one of the three groups. A power analysis (calculated using *G*Power*, version 3.1.9.7 [29] showed that a sample of at least 15 was required to detect a medium effect size (*ES*) of 0.5 (*α* = 0.05, 1 − *β* = 0.95) using a repeated-measures analysis of variance (*ANOVA*), in agreement with some previous studies [30,31]. The effect size of 0.5 was chosen given that this value was verified from studies investigated the effects of exercise on the variables of interest in our study [32,33,34].

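### Section 8 picks rank tests for every outcome on a false 30-participant rule, and the 0.95 power in section 2.2 belongs to a repeated-measures ANOVA that is not planned

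*Protocol article*

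**What the plan says.** **Protocol article, section 8 (Statistical Analysis).** Groups are compared by Kruskal–Wallis and visits are compared "between times using *Wilcoxon* or *Friedman* test". No other test of group or time is named. The reason given is "The non-parametric statistic was defined according to the “Central Limit Theorem” [63], in the sense that it will require 30 participants in the sample" for the data to be normally distributed. The same section says that "normality and homogeneity will be verified through the *Shapiro*–*Wilk* test and the *Levene* tests, respectively", but ties no decision to the result.

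**Section 2.2 (Participants).** The power calculation "showed that a sample of at least 15 was required to detect a medium effect size", with the settings "effect size (*ES*) of 0.5 (*α* = 0.05, 1 − *β* = 0.95", "using a repeated-measures analysis of variance (*ANOVA*), in agreement with some previous studies". The planned number is larger: "the sample will consist of the first 21 individuals who agree to participate in the program".

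**Elsewhere.** Section 2.1 gives three groups with equal allocation, so 7 each, without randomisation, measured at weeks 0, 12 and 24. In section 1, hypotheses (i)–(iv) concern change after 12 and/or 24 weeks of exercise, and (v)–(viii) concern differences between groups.

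**The concern.** Three things do not fit together.

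1. The stated reason is wrong. The theorem describes how the mean of repeated samples behaves. It sets no threshold of 30 and says nothing about the shape of 21 measurements.
2. The assumption checks are idle. Sample size has already fixed the choice, so no Shapiro–Wilk or Levene result can change it.
3. The sizing test is not the analysis test. The 0.95 is the power of an F test that section 8 does not plan, and nothing in the article gives the power of the rank tests.

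Many outcomes are continuous: torque, handgrip, walk distance, body composition, blood pressure. With about 7 people per group there is little power to spare. Friedman is the test that could cost most, because it reduces each person's three values to the ranks 1, 2, 3 and ignores the size of the change. Separate Kruskal–Wallis and Friedman tests also provide no group-by-time test and no adjustment for baseline, which matters when the groups are self-selected.

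**Working it through.** **Inputs from the article:** alpha 0.05, power 0.95, effect size 0.5, minimum 15 (section 2.2); 21 planned (section 2.2); k = 3 groups and m = 3 visits (section 2.1).

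**Assumed, because the article does not state them:** effect size is Cohen's f, within-person correlation rho = 0.5, and sphericity holds.

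**Step 1: reproduce the 15.** For the within-person effect, lambda = N·m·f²/(1 − rho), with df1 = m − 1 and df2 = (N − k)(m − 1).
- At N = 15: lambda = 15 × 3 × 0.25 / 0.5 = 22.5, df 2 and 24, power 0.984.
- The smallest N reaching 0.95 is 13, which rounds up to 15 for equal groups. The stated figure is reproduced.
- Other readings do not give 15. The group-by-time interaction needs 16 (18 balanced; power 0.948 at 15), the between-group effect needs 45, and f = 0.25 (the equivalent of d = 0.5) needs 43 to 45.

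So the 15 is best read as an F test for change over time.

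**Step 2: efficiency of Friedman.** Under normality its asymptotic efficiency against the F test is (3/π) × m/(m + 1) = 0.955 × 3/4 = 0.716.

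**Step 3: power of F and Friedman (simulated; asymptotic Friedman p).** Linear change and normal errors unless stated.

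| n in the test | f | rho | Data | F | Friedman | Loss (points) |
|---|---|---|---|---|---|---|
| 7 | 0.5 | 0.3 | normal | 57% | 46% | 11 |
| 7 | 0.5 | 0.5 | normal | 72% | 59–60% | 12–13 |
| 7 | 0.5 | 0.5 | normal, gain by week 12 then plateau | 72% | 57% | 15 |
| 7 | 0.5 | 0.7 | normal | 92% | 82% | 10 |
| 7 | 0.4 | 0.5 | normal | 52% | 42% | 10 |
| 7 | 0.25 | 0.5 | normal | 23% | 19% | 4 |
| 14 | 0.5 | 0.5 | normal | 98% | 91% | 7 |
| 15 | 0.5 | 0.5 | normal | 99% | 93% | 6 |
| 21 | 0.5 | 0.5 | normal | 99.9% | 98.8% | 1 |
| 7 | 0.5 | 0.5 | t, 5 df | 75% | 68% | 7 |
| 7 | 0.5 | 0.5 | t, 3 df | 80% | 80% | about 1 |
| 7 | 0.5 | 0.5 | lognormal | 82% | 90% | −8 |

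An exact Friedman p at n = 7 has attained size of about 0.027 and power of 48% in the base case, a loss of about 24 points. The article does not say that exact p-values will be used.

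**Step 4: the other rank tests (f = 0.5, normal errors).**
- Exact Wilcoxon signed-rank, week 0 against week 24, n = 7, rho = 0.5: linear change, 74% against 77–78% for the paired t test (3 to 4 points); plateau pattern, 62% against 65% (3 points).
- Kruskal–Wallis against one-way ANOVA, 3 groups of 7: 41.5% against 45.7% (about 4 points).

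**The case against.** The strongest reply is that the tests are valid and only the reason for them is wrong. Under the null, simulated rejection rates were 5.1% for Friedman and 4.8% for Wilcoxon, so error control is sound. Normality cannot be checked reliably with 7 per group, and several outcomes are bounded or probably skewed: the MMSE, the quality-of-life scale built on three-option items, pNN50 and LF/HF. Rank tests are a reasonable choice for those. This stands.

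The plan also names Wilcoxon as an alternative to Friedman, and hypotheses (i)–(iv) can be read as pairwise contrasts from baseline. Wilcoxon uses the size of the change. Under linear change its 74% matches the 72% of the three-visit F test. This stands too. A reader might infer from the 0.716 efficiency that the plan throws away a quarter of its information on change over time. The documents do not support that, because it is true only of Friedman and only near normality.

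The unit of analysis is not stated either. Pooling all 21 would make the Friedman loss about 1 point in the base case. That reading is less natural, since section 9 expects no change in controls. Pooling the 14 exercisers, which gives a loss of about 7 points, is more plausible.

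What the reply does not answer is the false rule, the idle assumption checks, and a stated power that belongs to a different test.

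**Conclusion.** The point holds as a wrong rationale and a mismatch between sizing and analysis, with a conditional cost in power. The loss is about 10 to 15 points only for a three-visit Friedman test within one group of about 7, with near-normal data, f of 0.4–0.5, rho of 0.3–0.7 and an asymptotic p-value. It is about 6 to 7 points at n = 14–15 (f = 0.5, rho = 0.5) or with t (5 df) errors at n = 7. It is about 3 to 4 points for Wilcoxon against the paired t test or Kruskal–Wallis against ANOVA, and nil or reversed for skewed data. Effect-size metric, rho and sphericity are assumptions throughout.

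Two stronger readings are not supported. One is that rank tests are an error in themselves; they control the type I error and suit some of these outcomes. The other is that, at the stated minimum of 15, a Wilcoxon test in a group of five could never be significant. The plan is for 21, about 7 per group, where the smallest exact two-sided p is 2/2⁷ = 2/128 = 0.016.

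**What to change.** - Delete the sentence in section 8 that links 30 participants to the Central Limit Theorem.
- Analyse continuous outcomes over weeks 0, 12 and 24 on the measured scale, using logs for skewed variables such as LF, HF and LF/HF. Use a repeated-measures ANOVA or mixed model with group, time and group-by-time, and a sphericity correction or unstructured covariance. This brings the analysis into the family used for sizing and supplies the missing interaction test for hypotheses (v)–(viii).
- A within-person permutation p-value may support the time effect. State that it assumes visits are exchangeable under the null, which unequal variances or correlations across visits would break.
- Keep Wilcoxon, Friedman and Kruskal–Wallis as sensitivity analyses, and for bounded scores such as the MMSE.
- Either give Shapiro–Wilk and Levene a stated purpose or describe them as descriptive only.
- If rank tests remain primary, say in section 2.2 that the 0.95 power applies to the ANOVA and not to them.

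Cost: a rewording before analysis and a little more programming, with no extra participants or measurements. SPSS 28 fits mixed models; a permutation p-value needs a short script. There is no power gain for strongly skewed variables left untransformed.

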#### 2.4.1. Indoor Training Program

The indoor PE program was carried out in a gym with weight machines. Seven heart rate monitors and seven gym towels will be required. The PE program was divided into four parts. Part I: playful game or shuttle run (5 to 7 min). Part II: aerobic training; Part III: strength training; Part IV: 4 static stretches/cool down. Table 1 shows the training program in detail.

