## 7. Participation Attendance/Adherence

Individual participation in each PE session will be scored with 0 (zero) if the participant does not attend or 1 (one) if the participant is present at the PE session and participates in it. At the end of the interventions, the participants who do not perform at least 75% of the sessions will be excluded from data processing.

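### Cohen's d with about seven people per group is biased away from zero on average, by about 7% between groups and 8–15% within groups; Hedges' g with a 95% CI would remove this at almost no cost

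*Protocol article*

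**What the plan says.** Section 8 (Statistical Analysis) names one measure for the size of differences: "The magnitudes of the differences will be examined using the" Cohen's d effect size. It gives no small-sample factor and no interval, and it does not say which standard deviation divides the difference. The tests beside it are rank-based. "The existence of significant differences between groups will be analyzed using the" Kruskal–Wallis test, and differences between times by Wilcoxon or Friedman. The reason given is that "it will require 30 participants in the sample to have a normal distribution".

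The group size follows from other sections:

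- Section 2.2: "the sample will consist of the first 21 individuals who agree to participate in the program".
- Section 2.1: three groups with equal allocation.
- Section 2.4.1, for the indoor programme: "Seven heart rate monitors and seven gym towels will be required".

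Together these point to about seven per group. Two features could make the analysed groups unequal or smaller. Section 2.1 forms the groups from participants' choices, "based on their interests and availability to be involved with PE programs", and section 7 adds that "the participants who do not perform at least 75% of the sessions will be excluded from data processing".

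**The concern.** Cohen's d divides a mean difference by an estimated SD. With few degrees of freedom, the average of one over the estimated SD exceeds one over the true SD, so d is on average further from zero than the true standardised effect. The excess is negligible in large samples but not at seven per group, and it is larger for a single group's change over time, where one group of seven may supply all the information on the SD. Hypotheses (i)–(iv) in the Introduction concern such changes.

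The stake is how the results are read and reused. Section 2.2 takes its own planning effect of 0.5 from earlier exercise studies, and later teams may treat this trial's values the same way. Required sample size scales roughly with 1/d². A study planned at the average uncorrected d would be about 12% too small between groups (0.936² = 0.876) and, at the upper end within groups, about 25% too small (0.869² = 0.755). Pooling across studies reduces random error but does not remove this bias.

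**Working it through.** The article gives no figure for this bias, so there is none to reproduce. Section 2.2's minimum of 15 comes from a power calculation and does not enter here. A true effect of 0.5 is used below only as an illustration.

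**Inputs.** 21 people (section 2.2) in three equal groups (section 2.1) gives 7 per group. No dropout rate is stated, so 5 and 6 per group are shown as assumptions.

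**Formula.** For roughly normal data, the average of d equals the true effect divided by J, where

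J(df) = Γ(df/2) / [√(df/2) · Γ((df − 1)/2)]

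and the average excess is 1/J − 1.

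**Between two groups of seven.** df = 7 + 7 − 2 = 12. J = Γ(6)/[√6 · Γ(5.5)] = 0.936, so the excess is 6.8%. If the SD is pooled over all three groups, df = 21 − 3 = 18, J = 0.958 and the excess is 4.4%.

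**Within one group of seven.**

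- Standardised by the SD of change or by the baseline SD: df = 6, J = Γ(3)/[√3 · Γ(2.5)] = 0.869, excess 15.1%.
- Standardised by the averaged pre/post SD: simulation with 200,000 replicates gives about 8% at an assumed pre/post correlation of 0.5, 11% at 0.8 and 13% at 0.9.

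**If the groups shrink.**

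| Analysed per group | Between two groups | Within group (SD of change or baseline SD) |
|---|---|---|
| 7 | 6.8% | 15.1% |
| 6 | 8.4% | 18.9% |
| 5 | 10.8% | 25.3% |

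**Absolute size at a true 0.5 and n = 7.** Between groups: 0.5/0.936 = 0.534, a shift of about 0.03. Within groups, upper end: 0.5/0.869 = 0.575, a shift of about 0.08.

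**Compared with sampling error.** For d = 0.5 at 7 v 7, the 95% half-width is 1.96 × √(14/49 + 0.25/28) = 1.06. The simulated sampling SD of a between-group d is about 0.60, so the bias is about 0.034/0.60, or 6% of one standard error. The simulated median is 0.509, and about 49% of estimates fall below the true 0.5.

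**Effect of the correction.** Multiplying d by J removes the average bias when the standardiser has the stated df. Because J is below 1 it also lowers the variance: the between-group sampling SD falls to about 0.60 × 0.936 = 0.56.

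**The case against.** The strongest reply is that this is a condensed article whose analysis plan is not shown. It neither states nor rules out a correction, and the standardiser, intervals and list of contrasts are details commonly left to that plan. This stands in part: their absence is not a defect, and an uncorrected d is only the plain reading of the measure's name. What remains is a stated choice of measure for which a better one exists.

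The second reply is that the bias is small beside the sampling error. That is true, and it sets the priority. A correction that costs nothing and also reduces variance is still worth making.

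Several stronger readings are tempting, but the documents do not support them:

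- A reader might infer that every reported effect will be inflated. The bias is an average; nearly half of single estimates fall below the true value.
- A reader might infer that the error always favours the programmes. It is multiplicative, so it enlarges unfavourable effects and control-group drift equally, and it vanishes when the true effect is zero.
- A reader might infer at least 15% within groups. That needs the SD of change or the baseline SD as standardiser, and the article specifies neither.
- A reader might fear results crossing a benchmark. The cut-offs printed in section 8 are for Spearman correlations; none is given for d.
- A reader might call d incompatible with rank tests. Section 8 also plans means and SDs as descriptives, which d summarises, and pairwise effect sizes can follow a three-group test. Hedges' g is mean-based too, so this argument would not favour it.

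**Conclusion.** The point holds as a low-priority improvement. With about seven per group, plain Cohen's d is biased away from zero on average by about 7% between two groups (about 4% with a three-group pooled SD) and by about 8–15% for within-group changes, depending on the standardiser. Smaller analysed groups would raise these figures, but the article does not say how much loss to expect. No test result changes, and at a true 0.5 the shift is well inside the sampling error.

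This rests on four assumptions: seven analysed per group, no correction applied, roughly normal data (which section 8 itself declines to rely on at this sample size) and, for the averaged-SD figures, pre/post correlations of 0.5 to 0.9.

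**What to change.** In section 8, replace Cohen's d with Hedges' g, defined as d multiplied by the small-sample factor for its degrees of freedom. Report it with a 95% CI and state the standardiser for between-group differences and for changes over time. The factor must match the standardiser: n − 1 degrees of freedom for the SD of change or the baseline SD, and the pooled degrees of freedom between groups. With the averaged pre/post SD the appropriate value depends on the pre/post correlation, so the approximation used should be named.

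The cost is one sentence in the plan and a few lines of analysis, with no change to data collection or sample size. The only downside is that reported effects become about 6–13% smaller at seven per group (1 − 0.936 = 6.4%; 1 − 0.869 = 13.1%), or about 4% smaller between groups if the SD is pooled over all three.
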